**3. Aims**

- - 1. To determine whether women experiencing DV and referred or self-referred to a specialist DV agency will have improved quality of life and mental health outcomes if they receive a psychological intervention alongside DV advocacy compared with advocacy alone
    2. To determine whether the psychological intervention is cost-effective.

**4. Objectives**

# To train eight domestic violence advocates, four at Bristol based advocacy organisation Next Link and four from Cardiff Women’s Aid to implement the intervention

4.2.1 To recruit **125** women to the intervention programme and **125** to the control arm

4.2.2 To follow up the women for 12 months from baseline measurements post-recruitment.

4.2.3 To administer baseline and 4 monthly follow up measures for 12 months from recruitment.

**5. Background**

5.1 Prevalence of domestic violence

Domestic violence is threatening behaviour, violence or abuse (psychological, physical, sexual, financial or emotional) between adults who are or have been intimate partners or family members. The 2004/5 British Crime Survey reported that 28% of women had experienced abuse from a partner or ex-partner at some time in their lives, with a 19% prevalence of physical assault and 24% sexual assault.1 Although acts of violence against men by women partners are not uncommon, these are generally less severe, with fewer long term consequences and mostly do not occur in a context of coercive control.2 Sexual violence against men by women partners is rare. The prevalence of domestic violence among women seeking health care is higher than in the general population. In the first primary care-based study in the UK, we found a lifetime experience of physical and sexual violence of 40%, with 17% of women experiencing domestic violence in the past year.3 Almost one third of women interviewed in Scottish primary care reported experience of domestic abuse at some point in their lives; for 45% of these women, the abuse lasted for over five years.4 Domestic violence is a major public health problem to which primary care historically has failed to respond adequately.5 The cost of domestic violence to the UK economy, including costs to the State, to employers and in human suffering is £23 billion.6 The issue of domestic violence is particularly important in the context of general practice, because of the extensive contact between women and primary care clinicians (90% consult over 5 years) and because women themselves identify primary care clinicians as the people from whom they would seek support.7

5.2 Mental health consequences

The impact of domestic violence has psychological parallels with the trauma of being taken hostage and subjected to torture.8 9 Over and above damage to physical10 11 and reproductive health,12 domestic violence has long term detrimental effects on mental health. In Golding’s landmark meta-analysis13 of studies, mostly from north America, measuring the relationship between domestic violence and mental illness, she reported increased risks for a range of conditions:

OR (95% c.i.)

- depression: 18 studies 3.8 (3.2 to 4.6)
- PTSD: 11 studies 3.74 (2.1 to 6.8)
- alcohol abuse: 9 studies 5.6 (3 to 9)
- suicidality: 13 studies 3.55 (2.7 to 4.6)

Our UK based study of women with a lifetime experience of domestic violence attending general practices in east London14 found odds ratios greater than three for depression, anxiety and PTSD and greater than two for suicide attempt, use of illegal drugs and alcohol abuse.

Self-harm has become of increasing concern in the UK particularly in young Asian women, linked to experiences of domestic violence and forced marriage[[1]](#endnote-2). Black and Asian women are at considerably more risk of attempting suicide, with prevalence ratios 1.6 times that of white women and 2.5 times that of Asian men, rising to 2.5 and 7 respectively for young Asian women (under 30, but often married). Domestic violence has been identified in 49% of suicide attempts made by black women compared to 22% of suicide attempts by white women.[[2]](#endnote-3)

Domestic violence may be the single most important cause of female suicidality.

5.3 Psychological interventions

Although there is some evidence of spontaneous improvement in mental health and quality of life of women who have left an abusive partner, mental health problems persist for years.15. We have systematically reviewed the evidence for domestic violence advocacy and psychological interventions on quality of life and mental health outcomes.16 17. Globally, there are only six controlled studies of individual psychological interventions for women who have experienced domestic violence, *none* in the UK and only three measuring depression outcomes. The six studies demonstrated modest) improvements (effect sizes ranged from 0.25 to 2.33) in psychological outcomes including depression, PTSD and self-esteem. Two randomized controlled trialsof individual cognitive therapy based interventions for women with PTSD who were no longer experiencing violence showed significant improvement in PTSD symptoms, but this cannot be extrapolated to women suffering from other mental health conditions nor women still in abusive relationships.

Clinical research with survivors of domestic violence (Herman 1992) distinguishes between stages of recovery for women who have experienced physical or sexual violence. Zimmerman (2006) recommends a three step process: crisis/emergency intervention; support for women’s recuperation and psychological adjustment; and care for long-term symptom management. As such, the initial needs of women at risk of further violation are to gain safety and security. (Foa & Meadows, 1997). Those who are secure can then process emotional and psychological sequelae. However, there is also a distinction between short-term symptoms, which can be resolved with help and longer-term symptoms or vulnerability, which may be much less amenable to change.

5.3 DV-competent therapy

Women with a recent history of domestic violence have mental health needs that are not being met in primary care or mental health services. Standard psychological interventions such as counselling and CBT that are not adapted to the specific needs of this vulnerable group are not effective and potentially dangerous. The NICE 2005 guidelines on the management of depression highlight the need for trauma focused psychotherapy in severe complex cases. We have developed an intervention (the Refuge model) designed and piloted by [name] and colleagues with a sample of 106 women within refuge settings18;19 funded by the Department of Health (section 64 funding programme). This intervention has not yet been tested with community populations. Using the clinical outcomes in routine evaluation-outcome measure (CORE-OM) measure, they found a reduction of mean total CORE score from 1.72 to 1.34 (clinical cut off = 1.29).

The Refuge model draws from different concepts and technical strategies within cognitive-behavioural, experiential, dynamic, psycho-educational and feminist theories. Theoretical and technical choice affords the offer of alternatives based on the question: ‘What would be the best approach with this (client) with this problem in this setting at this time?’ 20 The approach is practical and eclectic, because no single psychotherapy can provide an adequate breadth of interventions 21 and is informed by very brief intervention models 22

5.4 DV-competent therapy delivered by domestic violence advocates

Within the UK, there is a network of domestic violence advocacy services, most affiliated to the Women’s Aid Federation. Specialist domestic violence advocates provide support to women who are referred from other services or self-referred and help them access resources in the community, including legal advice, housing and financial support. Generally they do not have a background or training in psychological therapies and do not provide counseling or other therapies. In our research programme, we are currently conducting a cluster randomized controlled trial to improve identification of domestic violence survivors in general practice and referral to advocacy services. (IRIS: ISRCTN74012786). Although survivors are well supported by these services, their mental health needs are not being addressed. As discussed above, referral to standard counseling or mental health services is unlikely to be effective and is potentially dangerous, particularly if there is still contact with the perpetrator. With the appropriate training, domestic violence advocates can deliver a specialist trauma-focused intervention to women who are referred from primary care or self referred to their partner domestic violence agencies.

**6. Intervention and control arms**

6.1 Training of advocates in psychological intervention

We will recruit four experienced advocates based at Cardiff Women’s Aid and four from Next Link, a Bristol-wide domestic violence agency that already collaborates in the IRIS trial and is a co-applicant in the NIHR applied research programme grant application. The seconded advocates will receive a 25-day training from [name]: five day blocks separated by a one week break after blocks two and four. The first module covers domestic violence awareness focussed on assessing the effects on psychological health and therapeutic principles working with this specialist population. The second module expands risk assessment and safety planning from a psychological perspective and delineates strategies for promoting recovery from Post Traumatic Stress Disorder. Subsequent sessions address psychological problems commonly presented by victims of intimate partner violence, including depression, anxiety, low self-esteem and managing loss. Once implementation starts, the advocates will attend fortnightly individual and monthly group supervision with [name].

6.3 Intervention arm

8 hour-long weekly sessions tailored to the needs of the individual woman and 1-2 booster sessions over the next 6 months. The advocates will provide time-limited interventions using a variety of (primarily) cognitive behavioural psychological techniques focussing within any one session on a specific presenting problem, such as hyper-arousal, sleeping difficulties or parenting problems. The advocate will empower the client to apply therapeutic strategies (such as diary keeping, challenging thoughts or goal setting) to promote recovery from each problem. While the intervention is manualised, each package will be tailored to promote needs-led flexibility in the problem focus and the order in which problems are addressed over an eight session contract. Common elements characterising all interventions will include a focus on domestic violence as an aetiological factor, post-traumatic stress as a framework and attention to the therapeutic alliance.

6.4 Control arm

This would be normal support from advocates, varying from a single session and referral to other agencies or regular meetings over a period of months.

**7. Trial design**

7.1 Participants

Women referred or self referred to Next Link or Cardiff Women’s Aid for domestic violence advocacy.

7.1.1 Inclusion criteria

- female
- aged => 16 years

7.1.2 Exclusion criteria

- psychotic illness
- unable to read English
- severe current drug or alcohol abuse
- currently attending counselling, CBT or other psychological treatments either in primary care or specialist psychiatric services

Current or past use of antidepressants or benzodiazepines is *not* an exclusion criterion.

7.1.3 Recruitment

Potential participants will be approached by the advocacy service intake worker at Next Link/Cardiff Women’s Aid who will ask all women meeting the inclusion criteria if they would be willing to speak a researcher from the University of Bristol about the research trial they are collaborating on. The contact details and safety preferences of women who consent to being contacted about the study will be transmitted to the researcher via telephone in the presence of the potential participant and will be kept strictly confidential. When initial telephone contact has been made with a woman, the researcher will arrange a face-to-face meeting with all women interested and eligible to take part, meeting the woman at a safe and convenient place. As part of the meeting, the researcher will give a detailed participant information sheet to the woman, explaining each point and answer any questions that the woman may have prior to seeking her written informed consent. Written consent for interviews and digital audio−recording of SPA sessions will be sought separately in addition from all women who have indicated their willingness to take part in interviews on the initial consent form.

Randomisation will be independent of the researcher and the participant will be informed which arm she is by the researcher. The advocates delivering the intervention will not have contact with the women in the control arm.

7.2 Randomisation

Participants will be randomly allocated, in a1:1 ratio to the intervention and control arms respectively via a computer program accessed remotely by the recruiting researcher. Information about allocation will be communicated to Next Link/Cardiff Women’s Aid by the researcher recruiting. Allocation will be stratified by whether women receive support from the safe house team or resettlement team at Next Link, or the refuge team or tenant support team at Cardiff Women’s Aid.

7.3 Setting

The intervention will be delivered either at premises of Next Link/Cardiff Women’s Aid, where private rooms are available, or at another venue deemed safe and convenient for the researcher and participant including participant’s homes or refuges.

7.4 Quantitative measures

7.4.1 Mental health measures

- CORE-OM: 34-item self-completed measure of psychological distress that provides a mean overall score (range 0–4) and four domain scores (well-being, problems, functioning and risk). This acceptable, standardised, valid and reliable outcome measure, with sensitivity to change, and UK normative data, was designed to assess efficacy and effectiveness across multiple disciplines offering psychological therapies.24
- PHQ-9
- GAD-7
- Sheehan’s (1986) Post-Traumatic Stress Symptom Questionnaire

The primary outcome of the trial will be a mental health measure, the CORE-OM, for which we already have pilot data in relation to the intervention. To detect a reduction of 0.4 SD on the CORE with a power of 80% at a 5% significance level would require 250 participants in the trial.

7.4.2 Abuse measures (baseline, 4 month, 8 month and 12 month follow up)

- Composite Abuse Scale (CAS): 30 item self-completed measure of partner abuse with good acceptability and reliability, with some evidence of criterion and external validity. 25 Measures partner lifetime and past 12 month partner abuse (can be adapted for more recent abuse)
- Child abuse measure (three questions)

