7.4.7 Cost data

- health service use of participants (self report)
- travel costs
- intervention training and delivery costs

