**8. Analysis**

- Intention-to-treat and per-protocol analyses, including all randomised patients for whom outcome data are available. Analysis of covariance with the one year CORE-OM score as the dependent variable, adjusted for baseline CORE-OM score and the minimisation variables. A standardised effect size will be calculated by dividing the effect size by the SD, pooled across the 2 groups with a sensitivity analysis for the effect of missing data with conservative assumption. To assess the stability of any treatment effect we will fit a mixed model for CORE-OM scores at 4, 8, and 12 months, adjusted for baseline CORE-OM and minimisation variables, using treated number of sessions as a fixed categorical effect. Binary and continuous secondary outcome measures will be analysed with logistic regression and analysis of covariance, respectively, adjusted for baseline CORE-OM scores and minimisation variables.
- With directly collected patient and treatment costs we will calculate cost-effectiveness from NHS and societal perspectives, using EQ-5D scores to generate quality adjusted life years and expressing these findings in terms of incremental cost per QALY gained.

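### The Composite Abuse Scale is scheduled at 4 and 8 months with no recall period shorter than 12 months fixed, and its baseline score is not among the planned covariates

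*Protocol*

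**What the plan says.** Section 7.4.2 lists the abuse measures for baseline and for the 4-, 8- and 12-month follow-ups. Of the Composite Abuse Scale it says: "Measures partner lifetime and past 12 month partner abuse (can be adapted for more recent abuse". Nothing in the protocol text at hand says whether the scale will be adapted, to what period, or at which visits.

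The spacing of visits is confirmed in section 4 (4.2.3): "To administer baseline and 4 monthly follow up measures for 12 months from recruitment".

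Section 8 analyses binary and continuous secondary outcomes by logistic regression and analysis of covariance, "respectively, adjusted for baseline CORE-OM scores and minimisation variables". The baseline value of the outcome itself is not in that list. Section 8 does not name the abuse scale, so this model applies to it only if it is treated as a secondary outcome. The primary outcome is the CORE-OM (section 7.4.1), analysed at one year (section 8).

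**The concern.** A follow-up measure in a randomised trial should describe the time since randomisation. Assessments four months apart and a recall of twelve months do not fit together: at the first two follow-ups the women would be reporting largely, or partly, on abuse that no allocation could have changed.

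At stake is what the trial can say about abuse at 4 and 8 months. A real change in either direction would look smaller than it is. The recall period is printed on the questionnaire, so it has to be settled before data collection. Once a woman has answered about twelve months, no later analysis plan can separate out the months since she was randomised.

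The missing covariate is a second, smaller matter. Earlier abuse is likely to explain part of the variation in later abuse, and the baseline score is collected anyway. Leaving it out of the model gives that information away.

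**Working it through.** The protocol gives no figure of its own on this point; its sample size calculation (section 7.4.1) concerns the CORE-OM only.

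**Inputs.** Visits at t = 4, 8 and 12 months and a recall of 12 months (section 7.4.2). Assumption: baseline coincides with randomisation.

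**1. Share of the recall window before baseline**, (12 − t)/12:

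- 4 months: 8/12 = 67%
- 8 months: 4/12 = 33%
- 12 months: 0/12 = 0%

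A recall of the past 4 months gives 0% at all three visits. A lifetime recall includes abuse before baseline at every visit.

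**2. Effect on the difference between arms.** Treat the window score as a time-weighted average of abuse before and after randomisation (assumption). Randomisation makes the part before baseline equal in the two arms on average, so it cancels from the expected difference. What remains is t/12 of the true difference:

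- 4 months: 4/12 = 33%
- 8 months: 8/12 = 67%
- 12 months: 12/12 = 100%

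**3. Illustration: the intervention truly halves abuse relative to control after randomisation.** Let abuse before baseline be 1 unit per month and the score be proportional to abuse in the window (assumption).

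- Control stays level. At 4 months the window totals are 8 + 4 = 12 and 8 + 2 = 10, an apparent reduction of 1 − 10/12 = 17%. At 8 months: 1 − (4 + 4)/12 = 33%.
- Control also halves after entry. At 4 months: 1 − (8 + 1)/(8 + 2) = 10%. At 8 months: 1 − (4 + 2)/(4 + 4) = 25%.

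A true 50% reduction would therefore appear as 10–17% at 4 months and 25–33% at 8 months.

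**4. Precision given up without the baseline abuse score.** Let r be the correlation between baseline and follow-up abuse scores after allowing for the covariates already in the model. Adding the baseline score multiplies the residual SD by √(1 − r²). The protocol gives no r; over an assumed range:

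- r = 0.3: √0.91 = 0.95
- r = 0.5: √0.75 = 0.87
- r = 0.7: √0.51 = 0.71

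The standard error of the abuse comparison would be about 5% to 29% smaller with the covariate. This holds at 12 months as well as at 4 and 8, and whichever recall is used.

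**The case against.** **The sentence describes the instrument, and its parenthesis shows that a shorter recall had been considered.** This is fair. The protocol does not say that the 12-month form will be used at 4 and 8 months, so the dilution is conditional. But the only recall periods it names are lifetime and twelve months, and the choice cannot be left to an analysis plan.

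**Abuse is peripheral.** Section 3 names quality of life, mental health and cost-effectiveness. The abuse scale is tied to none of these and is not named as a secondary outcome. This stands, and it limits the importance of the point.

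**A reader might infer that the recall period destroys power for abuse.** Such a figure would need an assumed effect, and the 0.4 SD in section 7.4.1 is stated for the CORE-OM alone. It would also be charged to the wrong cause. In the averaging model above, with equal spread before and after and correlation rho between them, adjusting for abuse before randomisation leaves a residual SD of (t/12) × √(1 − rho²). A true effect of 0.4 SD is diluted to 0.4 × (t/12), so the standardised effect is 0.4/√(1 − rho²), in which t/12 cancels. In that idealised model the power loss disappears with the covariate alone, although the raw difference stays diluted. Power figures are therefore not evidence about recall.

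**A reader might also infer that the trial has no record of harm events and no check of the CORE-OM risk items.** That would rest only on absence from the visible text, and pages have been removed. The text at hand cannot support it.

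**Conclusion.** The point holds in a limited form. The protocol leaves the recall period open at two of the three follow-up visits. If the 12-month form is used there, the absolute difference between arms in abuse since randomisation is diluted to about one third at 4 months and two thirds at 8 months. These fractions rest on baseline coinciding with randomisation and on a score that averages abuse over the window.

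This is attenuation at two interim visits of a measure that is not primary. It does not favour either arm. It would be wrong to read it as casting doubt on the primary one-year CORE-OM analysis, or on a 12-month abuse comparison with 12-month recall, whose window is exactly the year after baseline.

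The omission of baseline abuse from the section 8 covariates is a separate loss of precision at all three visits. It applies if the scale is analysed under the rule for secondary outcomes, and its size depends on a correlation that the protocol does not give.

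**What to change.** 1. In section 7.4.2, state that at 4 and 8 months the Composite Abuse Scale asks about the period since the last scheduled assessment (four months). Keep the 12-month recall at baseline and at 12 months.
2. In section 8, add the baseline Composite Abuse Scale score as a covariate in the model for this outcome, beside those already listed.

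**Cost.** One sentence on recall, two printed versions of the form, and one extra covariate from data already collected. The 4- and 8-month scores will not be directly comparable in level with the baseline and 12-month scores. Baseline abuse should therefore enter as a covariate and not be used for change scores, and a trend in level across visits should not be read from the raw scores. The comparison between arms at each visit is unaffected by this, because both arms answer the same form.
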